## Abstract

**Background:**

Cardiovascular disease has become a major health problem, and it has been associated with both environmental and genetic factors. Studies have shown that the Mediterranean Diet (MeDiet), or its components such as nuts and olive oil, may be strongly associated with the improvement of cardiovascular risk factors in specific populations. The purpose of the GENUTRI study is to investigate the interaction of genetics with cardiovascular risk factors in a non-Mediterranean population with coronary artery disease (CAD) according to three different diets: rich in pecan nuts, in extra-virgin olive oil or a control diet.

**Methods/design:**

The GENUTRI study is a single-center, randomized, open-label, parallel-group, 12-week pragmatic clinical trial conducted in patients aged 40 to 80 years and diagnosed with CAD. A standardized questionnaire will be applied to data collection and a blood sample will be obtained for lipid, glycemic and inflammatory profile evaluation. Polymorphisms in the *CD36* and *STAT3* genes will be detected using the TaqMan® SNP Genotyping Assay. Patients will be allocated in three groups: group 1: 30 g/day of pecan nuts; group 2: 30 ml/day of olive oil; and group 3: control diet. The primary outcome will consist of changes in LDL-cholesterol (in mg/dl) after 12 weeks of intervention.

**Discussion:**

Studies have shown the beneficial effects of diets rich in nuts and olive oil mainly in the Mediterranean population. GENUTRI is a clinical trial focusing on the effects of nuts or olive oil supplementation in Brazilian individuals. Additionally, we will try to demonstrate that genetic polymorphisms linked to cardiovascular disease may modulate the effects of different diets on biochemical and inflammatory markers among these subjects.

**Trial registration:**

ClinicalTrials.gov Identifier: NCT02202265 (registered on 18 July 2014: first version).

## Background

According to the World Health Organization (WHO), cardiovascular disease is the leading cause of mortality worldwide, being responsible for 18 million deaths annually [1]. Coronary artery disease (CAD) is considered the main cardiovascular disorder, and approximately 46 % of the cardiovascular mortality in men and 38 % in women is attributed to CAD [2].

About 80 % of all mortality from cardiovascular disorders could be prevented if obesity, unhealthy diet and physical inactivity were excluded from the general population [3] and the adherence to a higher-quality diet is associated with decreased mortality risk [4]. In this meaning, the Mediterranean Diet (MeDiet), which incorporates the traditional healthy living habits of people from countries bordering the Mediterranean Sea, has been consolidated as a dietary pattern highly associated with reduced cardiovascular [5] and mortality risk [6]. Besides, adherence to a MeDiet pattern seems to be strongly related to cardiovascular protection when compared to low-fat dietary patterns [5, 7].

Nuts (rich in polyunsaturated fatty acids – PUFA) and olive oil (rich in monounsaturated fatty acids – MUFA) are highly used in the Mediterranean cuisine [8]. Despite regular intake of nuts and olive oil seems to be inversely associated with cardiovascular risk factors, CAD and mortality in some populations [9–11], these effects have not been observed in all studies, mainly in non-Mediterranean countries [12, 13]. The PREDIMED (PREvención con DIeta MEDiterránea) study was a larger clinical trial that randomly assigned participants who were at high cardiovascular risk (but with no cardiovascular disease) to one of three diets: a MeDiet supplemented with extra-virgin olive oil (minimum 50 ml/day) or with mixed nuts (30 g/day), or a control diet (low-fat diet). The PREDIMED study showed that both MeDiets supplemented with extra-virgin olive oil or nuts reduced, by approximately 30 %, the incidence of major cardiovascular events in a European population [5].

Beyond unhealthy diet, genetic factors are strongly associated with the development and the progression of cardiovascular diseases [14]. The *CD36* (CD36 molecule (thrombospondin receptor)) and the *STAT3* (signal transducer and activator of transcription 3 (acute-phase response factor)) genes are both related to pathways involved in the genesis of CAD [15, 16], and may interact with dietary factors. The single-nucleotide polymorphism (SNP) rs1761667 G>A in the *CD36* gene has been associated with a higher intake of dietary fats and obesity [17], and the SNP rs8069645 A>G in the *STAT3* gene seems to interact with higher saturated fat intake and increases the risk for abdominal obesity [18]. However, the association of these SNPs with cardiovascular risk factors, such as lipid profile and inflammatory markers, and a possible interaction with different dietary fats are poorly understood in patients with CAD.

Therefore, we design a randomized clinical trial to investigate the interaction of genetics with cardiovascular risk factors in subjects with CAD who do not live in the Mediterranean region, according to dietary prescription with different supplementary fats used in the MeDiet.

## Methods/design

### Study design and centers

The GENUTRI study is a single-center, randomized, open-label, parallel-group, 12-week pragmatic clinical trial (blinded outcome assessment). The study population will include patients with the diagnosis of CAD identified during a period of hospitalization in the Institute of Cardiology of Rio Grande do Sul (IC/FUC), Brazil, and outpatients who volunteered for the trial. The randomization, allocation and follow-up procedures will take place at the outpatient Clinic of Nutrition.

### Study objectives

The primary objective of this randomized-controlled clinical trial is to evaluate the effect of three dietary approaches on metabolic, inflammatory and anthropometric profiles in patients with CAD after 12 weeks. The secondary objective is to detect an interaction of patients’ response to these three dietary approaches with polymorphisms in the *CD36* and *STAT3* genes.

### Participants

Inclusion criteria: patients aged 40–80 years diagnosed with CAD who have signed an informed consent to participate. CAD was defined by a diagnosis of previous myocardial infarction, acute coronary syndrome or typical angina pectoris. Myocardial infarction was defined according to the universal definition of myocardial infarction [19].

Exclusion criteria: psychiatric disease; morbid obesity (body mass index (BMI) ≥40 mg/m^2^); expectancy of life less than 6 months; pregnancy or lactation; renal failure (in dialysis); congestive heart failure; prior organ transplantation; uncontrolled hypo/hyperthyroidism; wheelchair-dependant individuals; use of vitamin/nutritional supplements; chronic use of nonsteroidal anti-inflammatory drugs; and concomitant participation in another experimental study.

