### Study protocol

Patients with CAD who have been hospitalized in our institution and/or those submitted to coronary interventions for CAD will be invited by telephone calls to participate in the study. For the individuals who meet the inclusion criteria and are eligible for the trial, an appointment will be scheduled with the researchers’ staff (physicians and nutritionists). Voluntary individuals who contact the investigators and who meet the inclusion criteria will be also scheduled. All individuals will be advised by telephone to fast overnight for 8 hours before the meeting.

After checking all exclusion criteria and signing the informed consent, a blood sample will be collected and the subjects will undergo a baseline cardiology assessment. A structured questionnaire containing demographic, socioeconomic and educational data will be administered. Medical history (including previous outcomes and drug prescriptions) and behavior data, such as smoking, alcohol intake and level of physical activity will be collected. Blood pressure levels will be evaluated; anthropometric data (weigh, height, waist, hip and neck circumferences) and records about actual dietetic consumption will be assessed.

After randomization and once allocation has been completed, the patient will be appropriately advised according to the intervention designated: pecan nut supplementation diet, olive oil supplementation diet or a control diet. Patients will be followed for a period of 3 months (12 weeks), and follow-up visits will be scheduled at 30 days, 60 days and 90 days (final appointment), when blood will be collected for laboratory analyses. Figure 1 shows all procedures and its periodicity during the trial according to follow-up visits. The patients will be reminded and prompted regarding the follow-up visits and the interventions by telephone calls.

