#### Clinical and behavioral variables

Medical history: data on CAD specifications, history of present illness, past medical history, history of previous outcomes (i.e., heart attack and stroke) and current medications will be collected during the patient interview. Hypertension, type-2 diabetes mellitus and dyslipidemia will be considered present according to previous diagnosis and/or the use of medications to treat each of these conditions.

Blood pressure: systolic and diastolic blood pressure will be evaluated using an automatic validated monitoring device (OMRON® HEM-7200) with an adequately sized cuff to the arm circumference, according to the guidelines [23].

Body weight and height: weight (kg) will be measured with participants barefoot, wearing minimal clothing, and standing at the center of a digital platform scale; height (cm) will be obtained with participants barefoot in the standing position, and with both arms hanging freely at the side with palms facing thighs.

Waist, hip and neck circumferences: waist circumference (cm) will be obtained with a plastic, flexible measuring tape at the middle point between the lower costal margin and the iliac crest in a perpendicular plane, with the patient standing on both feet, approximately 20 cm apart, and with both arms hanging freely. Hip circumference will be measured at the level of the widest circumference over the buttocks with the research assistant kneeling at the side of the participant, so that the level of maximum extension can be seen. Neck circumference (cm) will be measured with the head straight and eyes staring forward, horizontally, 1 inch above the laryngeal prominence.

Smoking and alcohol intake: smoking will be defined as a categorical variable (never, current or past smoking) and excessive alcohol intake will be detected if participants have a consumption of 30 g or more and 15 g or more of ethanol a day for men and women, respectively [26].

Dietary evaluation: food intake will be evaluated by means of 24-h dietary recalls (24-HDRs). Caloric intake and nutrients will be estimated by Avanutri Revolution® Nutritional Evaluation software (Rio de Janeiro, Brazil) [27].

Physical activity: levels of physical activity will be evaluated according to the International Physical Activity Questionnaire (IPAQ) short version [28] translated and validated into the Portuguese language.

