### Outcome measures

#### Primary outcome

The primary outcome measure will consist of changes in LDL-c (mg/dl) from baseline to 12 weeks.

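### Entry soon after a coronary event is allowed without stable lipid-lowering treatment, and the LDL-c analysis does not fix baseline treatment as a covariate; the main cost is precision

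*Protocol article*

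**What the plan says.** All references are to the Protocol article.

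- **Eligibility (Participants).** "Inclusion criteria: patients aged 40–80 years diagnosed with CAD who have signed an informed consent to participate". The qualifying diagnoses follow: "CAD was defined by a diagnosis of previous myocardial infarction, acute coronary syndrome or typical angina pectoris". The exclusions that concern drugs or other studies are "use of vitamin/nutritional supplements; chronic use of nonsteroidal anti-inflammatory drugs; and concomitant participation in another experimental study". Statins, other lipid-lowering drugs, time since an event and time since an intervention do not appear.
- **Source of patients.** Study design and centers describes "patients with the diagnosis of CAD identified during a period of hospitalization", together with outpatient volunteers. Study protocol adds: "Patients with CAD who have been hospitalized in our institution and/or those submitted to coronary interventions for CAD will be invited by telephone calls". Randomisation takes place at the outpatient nutrition clinic.
- **Outcome (Primary outcome).** "changes in LDL-c (mg/dl) from baseline to 12 weeks". Under Laboratory variables, blood is drawn at baseline and after 12 weeks. No run-in is described.
- **Medication data.** Drug prescriptions are part of the baseline medical history (Study protocol), and "current medications will be collected during the patient interview" (Clinical and behavioral variables).
- **Analysis (Statistical analyses).** The 12-week change is compared between groups by ANCOVA. The covariates are described only as potential confounders, and the one example is a difference between groups at baseline. Lipid-lowering treatment is not named.

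**The concern.** A hospital stay for an acute coronary event, or a coronary intervention, is a natural occasion to start or change a lipid-lowering drug. The article lets such patients enter without a waiting period. If the baseline sample is taken while the drug effect is still developing, part of that patient's 12-week change has nothing to do with diet.

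The eligibility list reads as complete. It covers other background influences, such as supplements, chronic anti-inflammatory drugs and uncontrolled thyroid disease, but not the drug class that acts directly on the primary outcome.

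The main stake is precision. The trial is sized for a 13 mg/dl difference, and non-dietary LDL-c movement in a minority of patients widens the spread of the change score and allows chance imbalance between arms. A covariate measured at baseline could recover some of this, but the analysis text does not commit to one. Choosing covariates by observed baseline differences is also the weaker method: a variable deserves adjustment because it predicts the outcome, whether or not it happens to be unbalanced.

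**Working it through.** **Inputs from the Sample size section:** difference 13 mg/dl; α = 0.05, taken as two-sided because sidedness is not stated; power 80 %; 57 per group. No SD is given, so the figure of 57 cannot be confirmed or refuted. It can only be solved backwards.

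**Step 1: implied SD of the LDL-c change.**
- Normal approximation: SD = 13 × √(57/2) / (1.960 + 0.842) = 24.8 mg/dl.
- Two-sample t-test (noncentral t): SD = 24.56 mg/dl, variance 603.1. This value is used below.
- Other readings of the same inputs give 25.6 (three-group ANOVA with both diets equal), 27.9 (one-sided) and 28.6 (control against the two diets pooled).

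**Step 2: added variance.** Suppose a share p of patients has an extra, non-dietary LDL-c shift of m mg/dl during the 12 weeks, in all arms alike. The variance becomes 24.56² + p(1 − p)m². Neither p nor m is in the document. The assumed range is p = 5-20 % and m = 30-50 mg/dl. The calculation also assumes that the planning SD does not already contain such shifts.

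| p | m (mg/dl) | added variance | SD (mg/dl) | power, 57 per group |
|---|---|---|---|---|
| 0 | – | 0 | 24.6 | 80 % |
| 5 % | 30 | 0.05 × 0.95 × 900 = 42.75 | √645.9 = 25.4 | 77 % |
| 10 % | 40 | 0.10 × 0.90 × 1600 = 144 | √747.1 = 27.3 | 71 % |
| 20 % | 50 | 0.20 × 0.80 × 2500 = 400 | √1003.1 = 31.7 | 58 % |

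These are powers for an unadjusted pairwise comparison. The planned ANCOVA would do better to the extent that its covariates explain the shifts.

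**Step 3: chance imbalance.** The shifts add a component with standard error m√(2p(1 − p)/57) to a pairwise contrast. At p = 10 % and m = 40 this is 40 × √(0.18/57) = 2.2 mg/dl. Its expectation is zero under randomisation, and it is the same variance as in Step 2 seen from another side, not a further loss.

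**Step 4: what bias would require.** If the share of patients changing treatment after randomisation differed between arms by d, the contrast would move by d × m. With d = 5-10 points and m = 30-50 mg/dl, that is 0.05 × 30 = 1.5 to 0.10 × 50 = 5 mg/dl. The document contains nothing from which d could be estimated, so this is a conditional figure only.

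**The case against.** **Entry is not immediate.** Patients are telephoned, given an appointment and randomised as outpatients. The word for a past event in the CAD definition can be read as covering acute coronary syndrome too. Typical angina, old infarctions and volunteers also qualify. This stands: only part of the sample is affected, and its share is unknown. It does not remove the gap, because no minimum interval is set anywhere in the article.

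**Randomisation deals with drift present at entry.** This stands and decides the character of the point. A reader might infer that post-event drift or recent statin starts bias the diet comparison. They do not: three concurrent randomised arms share them in expectation, and the control arm carries the same drift.

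**Differential treatment changes are speculative.** A reader might infer from the open-label design that unblinded physicians will intensify treatment more in one arm. The Randomization and blinding section says that patients and those who evaluate and collect data know the diet. It does not say that these people prescribe. Samples are stored at −80 °C for later analysis, and the staff assessing biochemical outcomes are blinded. The text therefore does not show trial LDL-c values steering treatment during follow-up. The route is possible but not shown.

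**Some gaps cannot be judged.** The schedule of procedures is in Figure 1, which is not shown, so it cannot be said that medication changes at follow-up go unrecorded. A full covariate list and sensitivity analyses may be in an SAP. This stands for their absence. The basis for adjustment that the article does state, with baseline differences as its example, remains open to comment.

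**The size rests on assumptions.** True. At the mild end of the range, power falls only to 77 %. In favour of the concern, the planning data came from people at high cardiovascular risk and not from hospital-recruited CAD patients, so it is plausible that they lack this variation.

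**Broad entry suits a pragmatic trial.** This is a fair reason not to insist on new eligibility rules. It is no reason to leave a strong predictor of the outcome out of the model.

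**Conclusion.** The point holds as a matter of precision and pre-specification. The article allows entry soon after an acute event or intervention, sets no condition on lipid-lowering treatment, and measures the primary outcome as change from a single baseline sample, while its ANCOVA covariates are left open. Under the stated assumptions (implied SD 24.6 mg/dl, shifts not already included in it, 5-20 % of patients affected by 30-50 mg/dl, no adjustment), power falls from 80 % to 77-58 %. The direction is firm; the size is not, because share, shift and SD are all absent from the document.

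The document does not support a claim that the diet contrast is systematically biased. That would need treatment changes after randomisation to differ by arm, which nothing in the text shows. Adjustment for baseline variables would not remove such a difference if it occurred, so a table of changes by arm is still worth having.

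**What to change.** 1. **Fix the covariates in advance.** In the primary LDL-c ANCOVA, name baseline LDL-c and baseline lipid-lowering treatment. Add recent start or change of that treatment, and time since the last event or intervention, where these are recorded. This replaces selection by observed baseline differences. Baseline medication is already collected, so the cost is a sentence in the plan and some coding. The article does not state that event dates are collected, so time since event may be incomplete for the 120 patients who have finished.
2. **Tabulate lipid-lowering changes during the 12 weeks by arm**, using the existing 30-, 60- and 90-day visits. If the visit forms do not already ask, this costs one question. For completed patients it depends on the records.
3. **Label any analysis restricted to patients with unchanged treatment as supportive only.** It conditions on something that happens after randomisation, and the subset is itself selected if changes differ by arm.
4. **Optional, for the sponsor to weigh:** an eligibility condition for remaining recruits that treatment has been stable before the baseline sample. It would reduce noise, but later recruits would then differ from the 120 already completed, some would start later, and a pragmatic trial would be narrowed. Items 1 to 3 do not depend on it, and none of the four requires any change to patients' care.

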### Ethical aspects

All procedures will be conducted in accordance with the ethical standards for human subject research set forth in the Declaration of Helsinki and also with the Good Clinical Practice (GCP) guidelines [20]. Written informed consent will be obtained by researchers from all patients included in the trial. The project was approved by the Research Ethics Committee of the Institute of Cardiology (registration number UP. 4861.13) and is registered in the ClinicalTrials.gov database.

### Study protocol

Patients with CAD who have been hospitalized in our institution and/or those submitted to coronary interventions for CAD will be invited by telephone calls to participate in the study. For the individuals who meet the inclusion criteria and are eligible for the trial, an appointment will be scheduled with the researchers’ staff (physicians and nutritionists). Voluntary individuals who contact the investigators and who meet the inclusion criteria will be also scheduled. All individuals will be advised by telephone to fast overnight for 8 hours before the meeting.

After checking all exclusion criteria and signing the informed consent, a blood sample will be collected and the subjects will undergo a baseline cardiology assessment. A structured questionnaire containing demographic, socioeconomic and educational data will be administered. Medical history (including previous outcomes and drug prescriptions) and behavior data, such as smoking, alcohol intake and level of physical activity will be collected. Blood pressure levels will be evaluated; anthropometric data (weigh, height, waist, hip and neck circumferences) and records about actual dietetic consumption will be assessed.

After randomization and once allocation has been completed, the patient will be appropriately advised according to the intervention designated: pecan nut supplementation diet, olive oil supplementation diet or a control diet. Patients will be followed for a period of 3 months (12 weeks), and follow-up visits will be scheduled at 30 days, 60 days and 90 days (final appointment), when blood will be collected for laboratory analyses. Figure 1 shows all procedures and its periodicity during the trial according to follow-up visits. The patients will be reminded and prompted regarding the follow-up visits and the interventions by telephone calls.

**Fig. 1 Fig1:**
[figure not shown]
Flow chart of the GENUTRI study

### Randomization and blinding

The randomization sequence (in blocks) will be computer-generated using the http://www.randomization.com/ website, and then organized in sealed opaque envelopes. After fulfilling the eligibility criteria during the first visit, participants will be randomly assigned by independent investigators to one of the three diet groups in accordance with the generated randomization list. Both patients and investigators responsible for evaluation and data collection will be aware of the assigned diet. The staff involved in the biochemical outcomes’ evaluation and in the statistical analysis will be blinded to group allocation.

